### Target Recruitment Sample Size

This is explicitly a development project phase, and as such the analysis is intended to produce pilot data to support and inform the design of a future larger definitive trial of remote monitoring in DMARD tapering. To determine the required sample size for the current study, our primary focus lies in testing whether the area under the curve (AUC) derived from the risk prediction model is significantly greater than a cut-point of 0.6. Assuming a true AUC of 0.8 and flare rate of 50%, we will be able to reject the null hypothesis (H0: AUC ≤0.6) with 90% power and a 2-sided type I error rate of 0.025 with a target recruitment size of 100 patients.

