The model will be generated at weekly landmark times throughout follow-up. At each landmark, the model will use all accelerometry data collected up to that time to estimate the probability of clinician-defined flare occurring within the subsequent 14 days. Weekly updating allows risk estimates to be refreshed throughout DMARD tapering and provides clinically actionable information to support decisions regarding continuation or modification of tapering.

We will also evaluate the accuracy of the model’s flare predictions for each prediction time window against patient-reported flares derived from the RA-FQ, based on responses to the yes or no question about current flare status. Patient-reported flare status will serve as the reference standard. Model-predicted flares will be compared against patient reports to calculate sensitivity, specificity, and agreement (Cohen κ). It helps to assess how well the model’s predictions align with patient perception.

Sensitivity: proportion of patient-reported flares that are correctly predicted by the model (true-positive rate); higher values, close to 100%, are desirable.Specificity: proportion of patient-reported nonflares that are correctly identified as no flare by the model (true-negative rate); higher values, close to 100%, are desirable.Agreement: measured using Cohen κ to quantify concordance between model-predicted and patient-reported flares; higher values, close to 1, indicate stronger agreement beyond chance.

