### Secondary Analyses

Our secondary objectives are to assess the usability and acceptability of continuous accelerometry monitoring using patient feedback questionnaires, retrospectively assess the accuracy of RA-FQ flare prediction vs clinically confirmed flare, and develop and evaluate a combined dynamic prediction model to investigate whether incorporating RA-FQ total scores alongside accelerometry-derived measurements improves the prediction of clinically confirmed flare.

Participant acceptability of continuous accelerometry monitoring will be assessed using a structured feedback questionnaire (Axivity Feedback Survey). The survey evaluates usability, comfort, technical issues, and impact on daily life (Section A: categorical and ordinal items), as well as overall satisfaction (0‐100 scale) and free-text comments (Section B).

Quantitative responses will be summarized descriptively. Categorical and ordinal items will be reported as frequencies and percentages, with graphical presentation where appropriate. The overall satisfaction score will be summarized using mean, SD, median, IQR, and range. Comparisons between time points (where applicable) may be explored using nonparametric tests. The free-text responses in Section B will not be analyzed, as they would require a qualitative analysis.

We also plan to refit the landmarking models for arthritis flare, using accelerometry data as longitudinal predictors and patient-reported flares from the RA-FQ as the outcome. This approach will help identify potential associations between accelerometry measures and patient-reported flares. Then, model-predicted flares will be compared against clinically confirmed flares to calculate sensitivity, specificity, and agreement (Cohen κ). This approach also allows us to assess how well the model’s predictions align with clinically confirmed flares.

Comparing the performance of these models with the ones mentioned in primary analyses will help assess whether accelerometry-derived signals are consistently predictive across different definitions of flare. If both models perform well, this will strengthen confidence that the signals are robust and not dependent on a single definition of flare.

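### For two comparisons the plan scores a continuous 14-day flare risk only by sensitivity, specificity and Cohen κ; adding AUC and making κ descriptive would be a cheap improvement

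*Protocol article*

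**What the plan says.** Primary Analyses has the model run at weekly landmarks "to estimate the probability of clinician-defined flare occurring within the subsequent 14 days". The output is therefore a probability.

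For the second primary subobjective in Textbox 1, the reference is the RA-FQ yes/no question on current flare, taken for each prediction window. The measures are those of a two-by-two table: "Model-predicted flares will be compared against patient reports to calculate sensitivity, specificity, and agreement (Cohen κ"). Of κ the section says "higher values, close to 1, indicate stronger agreement beyond chance".

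Secondary Analyses refits the landmark models with patient-reported flare as the outcome. It then says "model-predicted flares will be compared against clinically confirmed flares to calculate sensitivity, specificity, and agreement (Cohen κ"). The results are to be set against those of the primary models, to judge whether the accelerometry signals predict consistently under both flare definitions.

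Elsewhere the article uses probability-scale measures. Target Recruitment Sample Size rests on an AUC. The Abstract lists time-dependent discrimination and calibration for model performance in general. The combined-model paragraph of Secondary Analyses names discrimination and calibration. None of these is tied to the two comparisons above.

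**The concern.** Reducing a probability to flare or no flare discards the ranking of risk. Of the three measures left, κ is the only single summary of agreement, and it does not measure discrimination alone. It also moves with the proportion of windows that contain a flare and with the chosen cut.

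This matters in two places. A reader who takes the remark about values near 1 as the yardstick could judge a usefully discriminating model to be poor. And the two flare definitions are counted differently: the clinical outcome is a first confirmed event, while the RA-FQ item asks each week about a current state, which may persist. Their window shares will probably differ. If κ informs the comparison across definitions, a difference in flare frequency could be read as a difference in signal.

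**Working it through.** **Inputs from the article.** Target Recruitment Sample Size: "Assuming a true AUC of 0.8 and flare rate of 50"%, tested as "H0: AUC ≤0.6) with 90% power and a 2-sided type I error rate of 0.025" "with a target recruitment size of 100 patients". The prediction horizon is 14 days. Follow-up is 12 months in the Abstract, 9 months in Study Design, and up to 6 months as currently approved in Ethical Considerations. The main period before the optional extension is 12 weeks.

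**The plan's own figure.** With 50 flares and 50 non-flares, 2-sided 0.025, and null and alternative variances, 90% power needs 86 patients (Hanley–McNeil) or 90 (Obuchowski binormal). Power at 100 is 95.0% or 93.7%. The stated 100 is not reproduced exactly, but it errs on the safe side. An unstated 10% dropout allowance would give it: 90/0.90 = 100. This has no bearing on the point here, which takes from that section only the AUC of 0.8 and the 50% flare rate.

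**Assumptions added.** (a) The risk score is equal-variance binormal. (b) The 50% flare rate accrues at a constant rate over T days, so the share of 14-day windows with a flare is p = 1 − 0.5^(14/T). (c) The patient-reported share is not given, so a range is shown.

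**Formulas.** Separation d = √2 × z(0.8) = 1.190. At the Youden cut (d/2 = 0.595), Se = Sp = Φ(0.595) = 0.724. With q = p·Se + (1−p)(1−Sp), observed agreement is po = p·Se + (1−p)·Sp, chance agreement is pe = p·q + (1−p)(1−q), and κ = (po − pe)/(1 − pe).

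**Two cases at the Youden cut.**
- p = 0.0262 (T = 365): q = 0.0190 + 0.2688 = 0.288; po = 0.724; pe = 0.0075 + 0.6936 = 0.701; κ = 0.0229/0.2989 = 0.077.
- p = 0.50: q = 0.50; pe = 0.50; κ = 0.224/0.50 = 0.448.

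**Range at AUC 0.8, with κ also maximised over all cuts.**

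| Window flare share | Basis | κ, Youden cut | Highest κ, any cut |
|---|---|---|---|
| 2.6% | 50% over 12 months | 0.077 | 0.183 |
| 3.5% | 50% over 9 months | 0.099 | 0.209 |
| 5.2% | 50% over 6 months | 0.138 | 0.247 |
| 10.9% | 50% over 12 weeks | 0.240 | 0.325 |
| 20% | illustrative | 0.342 | 0.389 |
| 50% | illustrative | 0.448 | 0.448 |

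AUC, and sensitivity and specificity at the Youden cut, are the same in every row: 0.80, 72% and 72%. Only κ moves.

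**Across definitions.** If one definition had a 2.6% share and the other 20%, the same discrimination and the same cut would give κ of 0.08 and 0.34.

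**Does κ respond to discrimination?** Yes. At a 2.6% share the highest κ is 0.18 at AUC 0.80, 0.52 at 0.95 and 0.78 at 0.99.

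**The case against.** Several objections are sound and limit the point.

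- κ is not the sole judge. Sensitivity and specificity are reported beside it, and at the Youden cut would read about 72% each in every row of the table.
- The remark on values near 1 gives a direction, with no pass mark, test or decision attached. It is not repeated for the refit analysis.
- The AUC of 0.8 is an assumed true value in a test against 0.6. It is not tied to patient-reported flare, where discrimination could be better or worse.
- The 2.6% share is an incidence of first flare. The RA-FQ item records a current state that may last several weeks, so its share could be much higher.
- Secondary Analyses does not say that the cross-definition comparison rests on κ.
- The cut-off itself may properly be left to an analysis plan that is not shown, and its absence is not counted here.

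A reader might go further and infer that κ cannot approach 1 for rare flares however good the model is. That is false: a perfect classifier has κ of 1 at any share, and the figures at AUC 0.95 and 0.99 show κ rising. A reader might also argue that dichotomising loses power, but no test on κ is planned.

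What remains is that neither comparison names a measure of discrimination free of flare share and cut-off, although the article uses such measures elsewhere.

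**Conclusion.** The point holds as a worthwhile improvement to a primary subobjective and to the refit analysis. At an AUC of 0.8, κ cannot exceed about 0.18 to 0.45 across flare shares of 2.6% to 50%. It can therefore be low for a model with useful discrimination, and can differ between flare definitions when discrimination does not. These figures rest on the binormal assumption; the shares of 2.6% to 10.9% also rest on a constant flare rate.

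It would be tempting to conclude that a model performing as the sample size assumes will be reported as near chance. The documents do not support that. It depends on a flare share they do not give (at a 20% share the Youden-cut κ is already 0.34), and κ would not be read alone. The plan does not build in a wrong conclusion.

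**What to change.** In Primary Analyses (comparison with patient-reported flare) and Secondary Analyses (refit):

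1. Add the time-dependent AUC of the continuous 14-day risk against each flare reference, with 95% confidence intervals from resampling participants rather than windows. Add calibration where a model is scored against the outcome to which it was fitted.
2. Report sensitivity and specificity at one common operating point for all models and both flare definitions, for example sensitivity at 90% specificity.
3. Keep κ as a descriptive figure only, shown with the window flare share and the cut-off used, and drop the remark about values near 1 as its reading.
4. State that the comparison across flare definitions rests on the AUCs.

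The cost is analysis wording and slightly more analysis work. The predicted probabilities will exist anyway, no new data are needed, and the Abstract says outcome analyses await completion of recruitment and follow-up. The one loss is that κ no longer serves as the single agreement summary.

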### Secondary Analyses

Our secondary objectives are to assess the usability and acceptability of continuous accelerometry monitoring using patient feedback questionnaires, retrospectively assess the accuracy of RA-FQ flare prediction vs clinically confirmed flare, and develop and evaluate a combined dynamic prediction model to investigate whether incorporating RA-FQ total scores alongside accelerometry-derived measurements improves the prediction of clinically confirmed flare.

Participant acceptability of continuous accelerometry monitoring will be assessed using a structured feedback questionnaire (Axivity Feedback Survey). The survey evaluates usability, comfort, technical issues, and impact on daily life (Section A: categorical and ordinal items), as well as overall satisfaction (0‐100 scale) and free-text comments (Section B).

Quantitative responses will be summarized descriptively. Categorical and ordinal items will be reported as frequencies and percentages, with graphical presentation where appropriate. The overall satisfaction score will be summarized using mean, SD, median, IQR, and range. Comparisons between time points (where applicable) may be explored using nonparametric tests. The free-text responses in Section B will not be analyzed, as they would require a qualitative analysis.

We also plan to refit the landmarking models for arthritis flare, using accelerometry data as longitudinal predictors and patient-reported flares from the RA-FQ as the outcome. This approach will help identify potential associations between accelerometry measures and patient-reported flares. Then, model-predicted flares will be compared against clinically confirmed flares to calculate sensitivity, specificity, and agreement (Cohen κ). This approach also allows us to assess how well the model’s predictions align with clinically confirmed flares.

Comparing the performance of these models with the ones mentioned in primary analyses will help assess whether accelerometry-derived signals are consistently predictive across different definitions of flare. If both models perform well, this will strengthen confidence that the signals are robust and not dependent on a single definition of flare.

As another secondary analysis, we will develop a combined dynamic prediction model to investigate whether incorporating patient-reported symptom information alongside accelerometry-derived measurements improves the prediction of clinically confirmed flare. The model will incorporate both longitudinal accelerometry-derived measures and the RA-FQ total score available at or before each prespecified landmark time. The RA-FQ captures patients’ subjective experiences of symptoms, including pain, stiffness, fatigue, and function, whereas accelerometry provides device-derived quality metrics and physical activity measures. The performance of the combined model will be compared with that of the accelerometry-only model using measures of discrimination and calibration to evaluate the additional predictive value of the RA-FQ.

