**Secondary subobjectives**
Assess the usability and acceptability of continuous accelerometry monitoring using patient feedback questionnairesAssess retrospectively the accuracy of Rheumatoid Arthritis Flare Questionnaire (RA-FQ) flare prediction vs clinically confirmed flareDevelop and evaluate a combined dynamic prediction model incorporating longitudinal accelerometry-derived measurements and the RA-FQ total score to predict clinically confirmed flare and compare its performance with that of the accelerometry-only model

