#### Month 3 Visit (±1 Week)

At the week 12 visit, within a 1-week window, patients will be asked to verbally confirm their willingness to continue in the study, and any changes in concurrent medications and any adverse events (AEs) since the last clinic visit will be recorded. A researcher will then assess the 28-joint tender and swollen counts, patient visual analog scale, and physician visual analog scale required for DAS28-CRP disease activity assessment. The patient will complete an HAQ-DI questionnaire and an RA-FQ paper questionnaire, unless an online RA-FQ has already been completed within the previous 24 hours. Any paper questionnaires provided at the last visit and the Axivity AX6 devices from the previous study visit will be collected. If arthritis flare is confirmed, defined as a DAS28-CRP of at least 2.4 or at least 1 swollen joint, this will already have been treated appropriately during the concurrent ROADMAP clinic appointment, and the study investigator will record the patient’s estimated date of flare onset.

All patients will then be offered enrollment in the optional 12-week extension study. If the patient agrees, they will immediately enter the extension phase, be provided with 3 new Axivity AX6 devices and 1 wrist strap to wear for 28 days each in sequence on the nondominant wrist, or the dominant wrist if needed, and, if they are unable to access the online REDCap portal, they will also be given 12 additional paper RA-FQs to complete weekly; their next and final study visit will take place 12 weeks later, 84 days, according to schedule 6.3. If the patient declines the optional extension, they will exit the study at this visit and will be given a feedback questionnaire on the usability and acceptability of the AX6 devices together with a stamped addressed envelope for postal return to the study team.

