#### Ad Hoc Flare Visits (Throughout the Study)

Patients tapering their DMARDs in the ROADMAP clinic may request additional ad hoc visits outside the usual 3-monthly schedules if they suspect an arthritis flare. There is no limit to the number of ad hoc visits, although in practice only one ad hoc visit would usually be expected for a patient who experiences a flare. In these cases, the patient will contact the study team to report possible flare symptoms, and a study investigator will then contact the ROADMAP clinic administrative team to arrange a ROADMAP clinic appointment and book a study visit to coincide with it. At the start of the ad hoc visit, patients will be asked to verbally confirm their willingness to continue in the study. Any changes in concurrent medications and any AEs since the last clinic visit will be recorded. A researcher will then assess the 28 joint tender and swollen counts, patient visual analog scale, and physician visual analog scale required for DAS28-CRP disease activity assessment. CRP blood test results obtained during routine clinical care at the ROADMAP clinic visit will also be recorded for DAS28-CRP calculation. The patient will then complete an HAQ-DI questionnaire and an RA-FQ paper questionnaire, unless an online RA-FQ has already been completed within the previous 24 hours.

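### The analysis described for the RA-FQ accuracy objective evaluates an accelerometry model trained on RA-FQ labels, so the questionnaire itself is not set against clinically confirmed flare

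*Protocol article*

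**What the plan says.** Textbox 1 (Secondary subobjectives) sets out to assess "retrospectively the accuracy of Rheumatoid Arthritis Flare Questionnaire (RA-FQ) flare prediction vs clinically confirmed" flare. The opening of Secondary Analyses repeats the aim: "retrospectively assess the accuracy of RA-FQ flare prediction vs clinically confirmed flare". On plain reading the questionnaire is the index test and clinical flare is the reference.

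After the acceptability survey, Secondary Analyses says the team will "refit the landmarking models for arthritis flare, using accelerometry data as longitudinal predictors and patient-reported flares from the RA-FQ as the outcome". The evaluation step follows: "Then, model-predicted flares will be compared against clinically confirmed flares to calculate sensitivity, specificity, and agreement (Cohen κ"). The section then explains that comparing these models with the primary ones "will help assess whether accelerometry-derived signals are consistently predictive across different definitions of flare".

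The data for a direct comparison exist. The RA-FQ section describes a yes/no item on whether the patient believes a flare is present. Month 3 Visit has the patient fill in a paper RA-FQ at the visit "unless an online RA-FQ has already been completed within the previous 24 hours", and joint counts and visual analog scales are assessed at the same visit. The extension and ad hoc visits follow the same pattern.

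**The concern.** The objective and the analysis have different index tests. The objective asks what the questionnaire can do. The analysis asks what an accelerometry model can do when it has been taught to imitate the questionnaire. Anyone who follows the text as written ends with a sensitivity, a specificity and a κ for the second question and none for the first.

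This matters because Target Recruitment Sample Size describes the study as pilot work for a larger trial of remote monitoring. Whether a short weekly questionnaire detects or anticipates clinical flare bears directly on how much a wearable adds, and that is the figure left without an estimate.

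**Working it through.** **Step 1. Trace every use of the RA-FQ.** For each analysis in the protocol article, ask what is tested and against what.

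| Section | What is tested | Against what |
|---|---|---|
| RA-FQ (Descriptive Analyses) | nothing; symptom items are summarized | none |
| Primary Analyses | accelerometry model trained on clinical flare | RA-FQ flare item, as reference standard |
| Secondary Analyses, refit | accelerometry model trained on RA-FQ flare | clinically confirmed flare |
| Secondary Analyses, combined model | accelerometry plus RA-FQ total score | clinical flare, compared with accelerometry alone |
| Discussion, Principal Findings | model-based prediction | compared with patient-reported flare |

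No row has the RA-FQ alone as the test and clinical flare as the reference. The combined model comes closest, but it has no RA-FQ-only arm and so shows only the increment over accelerometry.

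**Step 2. What the refit estimates.** The documents give no accuracy figures for the RA-FQ or for the model, so there is no stated figure to reproduce. The values below are assumptions chosen for illustration.

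Let Se_Q and Sp_Q be the RA-FQ's sensitivity and specificity against clinical flare. Let Se_M and Sp_M be those of the refitted model against the RA-FQ label. If the model's prediction depends on clinical flare only through the RA-FQ label (conditional independence), the planned comparison gives:

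- sensitivity = Se_Q × Se_M + (1 − Se_Q) × (1 − Sp_M)
- specificity = Sp_Q × Sp_M + (1 − Sp_Q) × (1 − Se_M)

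Worked case, RA-FQ 0.80/0.90 and model 0.70/0.80:

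- sensitivity = 0.80 × 0.70 + 0.20 × 0.20 = 0.56 + 0.04 = 0.60
- specificity = 0.90 × 0.80 + 0.10 × 0.30 = 0.72 + 0.03 = 0.75

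The same formulas over a range (sensitivity/specificity):

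| RA-FQ vs clinical flare | Model vs RA-FQ | Planned analysis reports |
|---|---|---|
| 0.90/0.90 | 0.90/0.90 | 0.82/0.82 |
| 0.90/0.90 | 0.70/0.80 | 0.65/0.75 |
| 0.90/0.90 | 0.60/0.70 | 0.57/0.67 |
| 0.80/0.90 | 0.90/0.90 | 0.74/0.82 |
| 0.80/0.90 | 0.70/0.80 | 0.60/0.75 |
| 0.80/0.90 | 0.60/0.70 | 0.54/0.67 |

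**Step 3. Read the table.** With the RA-FQ held at 0.90/0.90, the reported sensitivity runs from 0.57 to 0.82 purely through the quality of the accelerometry model. Even a perfect questionnaire (1.00/1.00) would be reported at the model's own 0.70/0.80, since 1.00 × 0.70 + 0 × 0.20 = 0.70 and 1.00 × 0.80 + 0 × 0.30 = 0.80. The result cannot be read back as RA-FQ accuracy. Without conditional independence the size, and possibly the direction, of the gap changes, but the quantity still belongs to the model.

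**The case against.** The strongest reply is that the article never says the refit is meant to deliver the RA-FQ accuracy objective. It introduces the refit as an additional plan and gives it its own purpose, robustness across flare definitions. On that reading the refit is a legitimate separate analysis, and the simple cross-tabulation is merely undescribed, which a condensed article may leave to an analysis plan not shown here. One could also read RA-FQ flare prediction as prediction by a model trained on RA-FQ flares.

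Part of this stands. The link between objective and refit is inferred from the order of the section (three objectives, then acceptability, refit and combined model), and an unseen plan may hold the direct comparison. But the article does specify predictor, outcome, comparison and metrics, and the refit is the only one of its analyses that could fill the place of this objective. The lenient reading also strains the wording of Textbox 1, and the Discussion treats the RA-FQ as a way of detecting flare in its own right.

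A reader might infer more than the documents support:

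- **That the model's figures will be published as the questionnaire's.** Secondary Analyses attributes them to the model's predictions; nothing says otherwise.
- **That ad hoc visits bias the result.** Patients "may request additional ad hoc visits outside the usual 3-monthly schedules if they suspect an arthritis flare", which is close to what the flare item asks. But no pooled RA-FQ analysis is planned. Suppose half of flares were confirmed ad hoc with the item always positive, and sensitivity for the rest were 0.60. The total of 0.5 × 1.00 + 0.5 × 0.60 = 0.80 would simply be sensitivity over all confirmed flares, not a demonstrated bias.
- **That the combined model's gain is inflated.** It uses the total score, not the flare item, and flare must still be confirmed clinically. An effect is plausible but not shown.
- **That scheduled visits are the clean set.** Under Ad Hoc Flare Visits, a patient with a confirmed flare may leave the study, move to a new 12-week schedule that replaces the planned visit, or finish without the extension review. Scheduled visits are thus depleted of flares that patients had already recognized.

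**Conclusion.** The point holds as a mismatch between a stated secondary objective and the analysis written beside it. As described, the analysis yields the accuracy of an accelerometry model, and the RA-FQ's own accuracy against clinical flare gets no estimate anywhere in the article. The size of the distortion, were the one read as the other, is unknown; the tabulated illustration rests on assumed accuracies and conditional independence. The conclusion about which test is evaluated needs neither. The finding does not extend to biased ascertainment or to misreporting. It should be corrected but does not threaten the primary analysis. Confidence is tempered by the inferred link and the unseen analysis plan.

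**What to change.** 1. State a direct RA-FQ analysis under the secondary objective. At each follow-up visit where both are recorded, compare the current-flare item with clinically confirmed flare (sensitivity, specificity, κ) and the total score by ROC curve and AUC. Exclude baseline, because entry requires DAS28-CRP below 2.4. Use participant-clustered confidence intervals, since patients contribute several visits.
2. Because the objective speaks of prediction, also evaluate the weekly RA-FQs completed before the visit; same-visit answers show concurrent detection only.
3. Report all follow-up visits together, then scheduled and ad hoc visits separately. Note that ad hoc visits are triggered by suspected flare and that scheduled visits lack flares already confirmed ad hoc.
4. Keep the refitted accelerometry model as a robustness analysis across flare definitions, and do not label it RA-FQ accuracy.

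The cost is a small extra analysis; no new data are needed. By July 1, 2026, 16 of the target 100 participants had been recruited, and the main analysis waits for complete follow-up, so the change can still be prespecified.
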